### Randomization

2.6

In this trial, participants will be randomly assigned to either the TCM group or the control group in a 1:1 ratio using a random number generator (SPSS 16.0, SPSS Inc, Chicago, IL).

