#### JOA score

2.13.2

The JOA score indicates the severity of clinical symptoms. The improvement in JOA score is calculated according to the following equation:^[16]^ Improvement according to JOA score (%) = (score after completion of treatment − score before treatment)/ (29 − score before treatment) × 100 (the maximum possible score is 29). An improved JOA score ≥75% was classified as excellent, 50% to 75% as good, 25% to 50% as fair, and <25% as poor. The JOA score will be measured during each assessment visit (ie, at baseline and 3- and 6-month follow-up).

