#### Sample size calculation

2.13.3

The required sample size was calculated using G∗Power 3 software, developed by the Institute for Experimental Psychology (Heinrich-Heine University, Germany). For this trial, it was determined prospectively that α =0.05 and 1-β =0.90. Consistent with a previous trial on massage for LDH, a total of 150 participants will be included in this trial (75 in each group) to compensate for an anticipated dropout rate of 15%.

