### Data analysis

2.14

Statistical analysis will be performed using SPSS 16.0. Measured data such as JOA scores and the volume of the protrusion will be compared using Student *t-*test for matched data; whereas enumerated data, such as the improvement in the JOA score, will be compared using the chi-squared test or Fisher exact probability test. *P* <.05 will be considered significant for all statistical tests.

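### JOA improvement falls into four ordered classes, but the planned chi-squared or Fisher test ignores the order: valid, yet inefficient for this secondary comparison

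*Protocol article*

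**What the plan says.** Section 2.13.2 (JOA score) defines improvement as the gain in score divided by the gain still possible (29 minus the baseline score), times 100. It then grades the result: "An improved JOA score ≥75% was classified as excellent, 50% to 75% as good, 25% to 50% as fair, and <25% as poor". JOA is recorded at baseline, 3 months and 6 months and is a secondary outcome.

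Section 2.14 (Data analysis) handles JOA in two ways within one sentence. First, "Measured data such as JOA scores and the volume of the protrusion will be compared using" a Student t-test, described as one for matched data. Second, "enumerated data, such as the improvement in the JOA score, will be compared using the chi-squared test or Fisher exact probability test". The threshold is P "<.05 will be considered significant for all statistical tests". No ordinal or trend test is named.

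Section 2.6 (Randomization) says participants are "randomly assigned to either the TCM group or the control group in a 1:1 ratio", so the arms are independent groups.

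**The concern.** The four classes are ranked, and the clinical question is whether TCM moves patients towards the better ones. A chi-squared or Fisher test on a 2×4 table gives the same P value if the labels poor and excellent are swapped. It spreads its sensitivity over three degrees of freedom when the effect of interest lies mainly along one. The underlying quantity is also numeric, so grading it loses information before the test is run.

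At stake is a real functional benefit being missed in the class comparison. The numeric JOA analysis does not clearly make up for this: a matched-data t-test, read literally, compares before with after within an arm and may not compare the two arms at all.

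The class limits also overlap as written. Exactly 50% is in both good and fair, and no rule settles it.

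**Working it through.** **1. Inputs from the article.** Section 2.13.3 gives "a total of 150 participants will be included in this trial (75 in each group"), "to compensate for an anticipated dropout rate of 15"%, and "it was determined prospectively that α =0.05 and 1-β =0.90". Evaluable per arm: 75 × 0.85 = 63.75, taken as 64 (63 in step 4). The maximum JOA score is 29.

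**2. The plan's own figure.** The total of 150 cannot be recomputed because no effect size is given. Solved backwards, two-sided: n per arm = 2(1.960 + 1.282)²/d² = 21.0/d². With d = 0.58 this is 62.5, rounded up to 63, and 63/0.85 = 74.1, rounded up to 75. So 150 is consistent with a standardised difference of about 0.58. The article does not tie this calculation to JOA, so it gives no power figure for JOA to reproduce.

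**3. Simulation on the JOA scale.** Assumed, not from the article: whole-point JOA scores, baseline 13 (SD 3), improvement 55% (SD 27%), and a pure shift in the TCM arm. With 64 per arm and two-sided 0.05, power is about:

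| Shift (percentage points) | Four-class chi-squared | Wilcoxon on the classes | ANCOVA of JOA score on baseline |
|---|---|---|---|
| 0 | 5% | 5% | 5% |
| 10 | 33% | 49% | 53% |
| 13.5 (13.5/27 = 0.5 SD) | 55% | 73% | 77% |
| 15 | 66% | 81% | 86% |

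The first row shows that all three tests hold their level. At 13.5 points the chi-squared test gives up 73 − 55 = 18 points against the ordinal test and 77 − 55 = 22 points against ANCOVA. Pooling good with excellent into a 2×2 table gives about 57%.

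**4. Does it depend on the class distribution?** A normal shift cut into four classes, 63 per arm, was run for four control distributions (poor/fair/good/excellent, in %: 25/25/25/25, 10/20/35/35, 5/10/25/60, 40/30/20/10) and shifts of 0.3 to 0.58 SD. The chi-squared test lost 11 to 19 points against the ordinal test throughout. With even classes and 0.58 SD, power was 0.69 for chi-squared, 0.84 for the ordinal test and 0.90 for a t-test on the ungraded value. At 0.58 SD the pooled 2×2 table had 0.44 to 0.72, against 0.72 to 0.85 for the ordinal test.

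**5. Cost in patients.** For 90% power a 1-df test needs non-centrality 10.51 and a 3-df test 14.17: 14.17/10.51 = 1.35. For 80% power the figures are 7.85 and 10.90: 10.90/7.85 = 1.39. If the effect lies wholly along the order, the unordered test needs about 35 to 39% more patients for equal power.

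**6. Boundary at 50%.** With whole-point scores there are 30 + 29 + … + 2 = 464 non-worsening before/after pairs (baseline 0 to 28). Of these, 14 give exactly 50%, and 14/464 = 3%. Under the assumptions of step 3, about 4.7% of patients land there: 0.047 × 64 = 3 per arm. With the 13.5-point shift it is about 3.8%. At 75% the explicit lower limit of the top class points to excellent, and the 25% limit is clean.

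**The case against.** **JOA is also analysed as a score.** The sentence that sends the classes to chi-squared also sends JOA scores to a t-test. A reader might infer that the functional outcome as a whole loses power; the article does not support that. The loss concerns the class comparison. The t-test is only a partial answer, because its matched-data label leaves open whether it compares the independent arms.

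**The 2×4 table is inferred.** The article does not say that all four classes enter the test. They are, however, its only categorical form of JOA improvement, and pooling to 2×2 does not recover the power (steps 3 and 4). The point therefore holds under either reading.

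**The figures rest on assumptions.** The article gives no JOA mean, SD or expected effect. For an effect that is not a shift along the scale, the unordered test need not be weaker. This stands.

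**The boundary is minor.** Because exactly 50% can be reached from 14 of the 29 baseline values, a reader might infer that many patients are affected. That counts baseline values, not patients; step 6 puts it at about 4 to 5%. A reader might also infer that unblinded staff could place borderline patients as they wish. Section 2.7 (Blinding) has clinical efficacy assessed by someone masked to allocation, and the percentage comes from a fixed formula, so the documents do not support this.

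**Conclusion.** The concern holds in a limited form. The planned test is valid but inefficient for ordered classes. For an assumed pure shift of 13.5 points with 64 per arm, power is about 55% (57% if pooled), against about 73% for an ordinal test and 77% for ANCOVA. The direction was the same in every shift scenario examined, with losses of 11 to 19 points against the ordinal test across the distributions in step 4. The exact sizes depend on inputs the article does not give.

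This concerns one comparison of a secondary outcome. The primary MRI outcome and the stated 90% power are not directly affected. The double placing of 50% is a wording fault that touches few patients. Since the better methods use data already planned, this is a free improvement rather than the repair of an invalid analysis.

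**What to change.** - State that the main JOA comparison is a between-arm ANCOVA of the 6-month JOA score with baseline JOA as covariate. This also removes the doubt about the matched-data t-test for this outcome.
- If the improvement classes are compared, use an ordinal test (Wilcoxon rank-sum or a proportional-odds model) in place of chi-squared or Fisher.
- Define the classes as <25, 25 to <50, 50 to <75, and ≥75%.

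The cost is two or three sentences. No extra patients, visits or measurements are needed, and the methods run in the planned software.

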## Discussion

3

LDH commonly occurs in patients 20 to 40 years of age and results in acute symptoms of shooting and intractable pain in the low back and/or lower extremities.^[20]^ However, the prognosis of these patients is usually very good. Moreover, 70% of LDH patients have been reported to be free from sciatica at approximately 6 months after the first onset.^[20]^ Ultimately, conservative treatment may be the best option when radiculopathy is acceptable and cauda equina syndrome is absent.^[14,21]^

MRI studies have clarified the spontaneous resorption process of herniated discs, which is a major cause of the reduction of symptoms in LDH patients.^[20,22]^ Recent advances in MRI techniques have facilitated the examination of nerve tract fibers and the identification of symptomatic nerve tissue. The LDH resorption process has been demonstrated using sequential MRI, and this resorption process may be the reason for the relatively good prognosis in cases of LDH.^[23]^

Mechanisms relating to spontaneous disc regression have been described in the literature. The first mechanism used to explain spontaneous disc regression is that the signal intensity of the nucleus pulposus at the initiation of the hernia is higher than that in the original nucleus, and then decreases with time. The hydration of the nucleus pulposus at the initiation of the herniation is then rapidly followed by dehydration.^[24]^ The second mechanism is the resorption theory. The nucleus pulposus with hernia is considered to be a foreign body by the immune system, and the inflammatory process starts with neovascularization. The nucleus pulposus with hernia is then eliminated by enzymatic catabolism and phagocytosis.^[25,26]^ The third mechanism proposes that enzymatic degradation and phagocytosis of cartilaginous tissue occurs as a result of the disc regression inflammatory reaction and neovascularization of disc herniation.^[27,28]^ The vascular supply may play a major role in resorption of the disc material. The vascular mechanism of resorption involves a local reaction around the disc fragments, the proliferation of blood vessels, and the migration of the phagocytes to the disc material; matrix proteinases and increased cytokine levels play a role in the spontaneous regression process.^[29,30]^ If the above mechanisms can be activated through drugs, in particular TCM, this will undoubtedly both alleviate the suffering of patients and increase social benefits.

Some studies have reported the effectiveness of herbal medicine, which is the most popular form of complementary and alternative medical therapy for the treatment of LDH, either used alone or concomitantly with usual care.^[9,15,16]^ The limited quality and small sample sizes of the few trials that have been conducted to date have made it difficult to reach firm conclusions about TCM treatments. Well-designed randomized controlled trials are needed to examine the efficacy of TCM treatments for LDH. The purpose of the study planned here is to evaluate the basic clinical efficacy and safety data of TCM in the treatment of patients with LDH. The study should also help to establish whether TCM promotes the resorption of LDH.
